### Outcome

All prediction models have mortality as the predicted outcome (Table 1). In all three hospital cohorts, the outcome is defined as in-hospital mortality. In the primary care and nursing home cohorts, the outcome is defined as 28-day mortality.

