**Fig. 1 Fig1:**
[figure not shown]
Flowchart for inclusion of prognostic models for external validation

**Table 1 Tab1:** Overview of selected prognostic models

Model name	Derivation country		Pre-existing or COVID-19 specific	Derivation health care setting	Derivation population	Intended moment of use	Predicted outcome	Predictors		Model type
**GAL-COVID-19-mortality model** [18]	Spain		COVID-19 specific model	Primary care	Adults (≥ 18 years) with confirmed COVID-19 diagnosis	First presentation with COVID-19 infection at general practitioner	Mortality (no prediction horizon reported)	• Age • Sex • Lymphoma/leukemia • Liver disease • Dementia • Ischemic heart disease • Chronic obstructive pulmonary disease • Diabetes mellitus • Chronic kidney disease		Prediction model
**4C-Mortality Score** [19]	UK		COVID-19 specific model	Hospital	Adults (≥ 18 years) with confirmed COVID-19 diagnosis	At hospital admission for COVID-19 infection	In-hospital mortality	• Age • Sex • Respiratory rate • Peripheral oxygen saturation on room air • Glasgow Coma Scale • Urea • C-reactive protein • Number of comorbidities (counted as chronic cardiac disease, chronic respiratory disease (excluding asthma), chronic renal disease, liver disease, dementia, chronic neurological conditions, connective tissue disease, diabetes mellitus, HIV or AIDS, malignancy, obesity)		Points-based score
**NEWS2 + model** [20]		UK	Pre-existing risk stratification score updated for COVID-19 patients	Hospital	Adults (≥ 18 years) admitted to the hospital with a confirmed COVID -19 diagnosis	• At hospital admission for non-nosocomial patients (i.e., community-acquired COVID infection) • At the date of symptom onset for nosocomial patients. If the date of onset was unavailable the date of positive SARS-CoV-2 RT-PCR minus 4 days was used instead	ICU admission or death within 14 days of admission	• Age • Peripheral oxygen saturation • Heart rate • Systolic blood pressure • Body temperature • Alertness • Supplemental oxygen flow rate • Urea • C-reactive protein • Estimated glomerular filtration rate • Neutrophil count • Neutrophil/lymphocyte ratio		Prediction model
**Xie model** [21]		China	COVID-19 specific model	Hospital	Adults (≥ 18 years) admitted to the hospital with a confirmed COVID -19 diagnosis	At hospital admission for COVID-19 infection	In-hospital mortality	• Age • Lactate dehydrogenase • Lymphocyte count • Oxygen saturation		Prediction model

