**Wang clinical model** [22]		China	COVID-19 specific model	Hospital	Adults (≥ 18 years) admitted to the hospital with a confirmed COVID-19 diagnosis. Pregnant women were excluded	At hospital admission for COVID-19 infection	In-hospital mortality	• Age • History of hypertension • History of heart disease		Prediction model
**APACHE-II Score** [23]		USA	Pre-existing risk stratification score	Hospital	All newly admitted ICU patients	At admission to ICU	Mortality	• Age • Body temperature • Heart rate • Respiratory rate • Mean arterial pressure • Arterial oxygen tension • pH • Potassium • Sodium • Creatinine • Hematocrit • Leucocyte count • Glasgow Coma Scale • Chronic health evaluation		Points-based score
**CURB-65** [24]		UK, New Zealand, The Netherlands	Pre-existing risk stratification score	Hospital	Patients with community-acquired pneumonia	For triage at the emergency department	Mortality (30 days)		• Age • Alertness (new confusion) • Urea • Respiratory rate • Systolic blood pressure • Diastolic blood pressure	Points-based score
**SOFA Score** [25]		Unclear	Pre-existing risk stratification score	Hospital	All ICU patients	At admission to and during admission at ICU	ICU-mortality		• Arterial oxygen tension • Fraction of inspired oxygen ratio • Glasgow Coma Scale • Mean arterial pressure • Administration of vasopressors • Creatinine • Bilirubin • Platelet count	Points-based score

*COVID-19* Coronavirus disease of 2019, *ICU* Intensive care unit; *RT-PCR* Reverse transcription polymerase chain reaction, *SARS-CoV-2* Severe acute respiratory syndrome coronavirus

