### Statistical analysis

We will externally validate the eight COVID-19 prognostic models in the six cohorts of older patients with COVID-19, aiming to assess their predictive performance when transported from a general adult population to a specific older population. The performance of the GAL-COVID-19 model is assessed across the three healthcare settings. The GAL-COVID-19 mortality model was developed in a primary care setting (general practitioners) and will be validated across different settings (in hospitals, primary care, and nursing homes) [26]. The 4C Mortality Score, NEWS2 + model, Xie model, Wang clinical model, APACHE-II score, CURB-65 score, and SOFA score were developed in hospitalized populations and will be externally validated in the same setting. Evaluation and assessment of the predictive performance of the COVID-19 prognostic models will be performed in each cohort separately. The statistical analysis will be performed in R (version 4.0.0 or later) [27].

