#### Assessment of predictive performance

For each prognostic model, we will apply the model according to the authors’ original descriptions and evaluate its predictive performance. We will evaluate discrimination (the model’s ability to distinguish individuals who died after presentation with COVID-19 diagnosis from those who did not) and calibration (the agreement between predicted and observed mortality risks) in each cohort [32]. Discrimination will be assessed in all models by quantifying the area under the receiver operating characteristic curve, i.e., c-statistic [33], and pooled by taking the median c-statistic over imputed datasets and computing dispersion using the interquartile range [34].

Calibration will be assessed by visualizing the calibration of expected versus observed risk using LOESS-smoothed plots on stacked imputed data sets [35]. The GAL-COVID-19 mortality model, NEWS2 + model, Xie model, and Wang clinical model are model equations. For these models, calibration will be assessed in terms of the calibration-in-the-large coefficient and calibration slope [35]. The coefficients are again pooled on a log scale using Rubin’s rules in case of multiple imputed datasets [36]. For each performance measure, for each evaluated model, we will compute the point estimate, standard error, and 95% confidence interval.

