#### Decision curve analysis

Decision curve analyses will be performed to quantify the net benefit achieved by each model for predicting the originally intended endpoint across a range of risk thresholds ranging from zero to one [37].

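### NEWS2+ predicts ICU admission or death within 14 days but is to be calibrated and updated against in-hospital mortality, so its miscalibration could not be separated from the change of endpoint

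*Protocol article*

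**What the plan says.** - **Outcome section.** It states "All prediction models have mortality as the predicted outcome (Table 1") and then "In all three hospital cohorts, the outcome is defined as in-hospital mortality". It makes no exception for any model.
- **Table 1, NEWS2+ row.** The predicted outcome is "ICU admission or death within 14 days of admission".
- **Table 2.** NEWS2+ is validated in CliniCo, COVID-OLD and COVID-PREDICT, all hospital cohorts, and nowhere else.
- **Assessment of predictive performance.** Calibration is defined as agreement between predicted and observed risks of death. "The GAL-COVID-19 mortality model, NEWS2 + model, Xie model, and Wang clinical model are model equations", and for these four "calibration will be assessed in terms of the calibration-in-the-large coefficient and calibration slope".
- **Updating.** A model that shows miscalibration has its intercept updated and its performance assessed again.
- **Decision curve analysis.** The target is the "net benefit achieved by each model for predicting the originally intended endpoint".

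**The concern.** The sentence in Outcome is contradicted by the table it cites. The NEWS2+ outcome differs from in-hospital mortality in both event and horizon: it counts ICU admission as an event, and it stops at day 14. If NEWS2+ is calibrated against in-hospital death, part of any gap between predicted and observed risk comes from the endpoint and would appear in a cohort of any age.

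The Background hypothesises that models built for adults in general will underperform in older people, and the Statistical analysis section makes transport to that population the aim. A NEWS2+ calibration result would invite that reading without being able to support it. The intercept update would then refit the model to a different outcome under the name of recalibration. The decision curve section points to a different endpoint for the same model, so calibration and net benefit would not describe the same prediction task.

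**Working it through.** **1. The endpoint of NEWS2+, section by section**

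| Section | Endpoint that applies to NEWS2+ |
|---|---|
| Table 1 | ICU admission or death, 14 days |
| Outcome | In-hospital death |
| Assessment of predictive performance | Death, with calibration-in-the-large and slope |
| Updating | Not restated; follows from the calibration result |
| Decision curve analysis | Original endpoint, hence the 14-day composite |

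The Outcome section defines no 14-day composite in any cohort. The sensitivity analyses change the calendar period or move to 90-day mortality, so neither supplies it. Challenges and limitations does not mention the mismatch.

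**2. Direction of the effect**

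In-hospital mortality minus composite risk = P(in-hospital death without a composite event) - P(composite event without in-hospital death).

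- The first term is patients who die in hospital after day 14 and were not admitted to ICU by day 14. It raises the observed rate.
- The second term is mainly patients admitted to ICU by day 14 who leave hospital alive. It lowers the observed rate.

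Either term may be larger, so the sign cannot be told from the documents.

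**3. Size under assumed rates**

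The plan has no figure to reproduce here: it gives neither a composite rate nor an in-hospital death rate for these cohorts. All inputs below are assumptions.

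- The linear predictor is normal with mean m and SD 1.
- The model is perfectly calibrated for the composite: choose m so that the mean of expit(m + Z) equals the composite risk, where Z is standard normal.
- Calibration-in-the-large against mortality is the shift d that makes the mean of expit(m + d + Z) equal the in-hospital mortality.

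For 45% and 35%: a mean risk of 45% needs m = -0.243, and a mean risk of 35% needs m + d = -0.746. Hence d = -0.746 - (-0.243) = -0.50.

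| Composite | In-hospital mortality | Observed/expected | Calibration-in-the-large |
|---|---|---|---|
| 45% | 35% | 0.78 | -0.50 |
| 50% | 30% | 0.60 | -1.02 |
| 40% | 40% | 1.00 | 0 |
| 35% | 40% | 1.14 | +0.26 |

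**4. Sensitivity to the assumed SD**

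With no spread in the linear predictor, d is the difference of marginal logits: logit(0.35) - logit(0.45) = -0.619 - (-0.201) = -0.42. With SD 1.5 the same pair gives -0.59. The conclusion does not depend on the choice of SD.

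**5. After the fix**

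Against its own endpoint, the part of calibration-in-the-large due to the endpoint is zero by definition. What remains is age, case mix, period and measurement, which is what the study sets out to examine.

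**The case against.** **A common mortality outcome may be deliberate.** The declared aim is mortality prediction, and testing every hospital model on the same outcome makes them comparable. This stands in part: an analysis of NEWS2+ against in-hospital death is legitimate if it is labelled as a change of outcome. It does not rescue the sentence in Outcome, nor does it remove the conflict with the decision curve section.

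**Models are to be applied as their authors described.** That instruction concerns how predictions are computed. It does not override the outcome fixed for the hospital cohorts.

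**The size is assumed and could be nil.** This is correct. At equal rates the shift in calibration-in-the-large is zero, and neither size nor sign is established.

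**The reach is limited.** The finding concerns one model of eight, in three cohorts of six, and each model is evaluated separately in each cohort. Results for the other models are not affected by the NEWS2+ mismatch.

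**Two stronger readings are not supported.**

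- A reader might infer that NEWS2+ miscalibration would be due to the endpoint and not to older age. The documents do not show that: both could contribute and the design cannot tell them apart. Nor does the Updating section itself describe the update as an age correction.
- A reader might also infer a parallel error for APACHE-II and SOFA, because the hospital models "were developed in hospitalized populations and will be externally validated in the same setting" while Table 1 gives, for APACHE-II, "All newly admitted ICU patients". Table 1 lists the derivation setting of both scores as hospital, so the statement is not contradicted. Both are points-based scores, for which no calibration-in-the-large or slope is planned. At most, the plan could note that they were derived in ICU patients and are applied here to hospital cohorts not restricted to the ICU.

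**Conclusion.** The plan is wrong as written for NEWS2+. The outcome statement is contradicted by Table 1. Calibration and intercept updating follow the in-hospital mortality outcome, and the decision curves follow another. This rests on the text alone and needs no assumption.

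The consequence is that any NEWS2+ miscalibration would combine the endpoint change with age and case-mix effects in proportions that cannot be recovered. With assumed rates and a linear predictor SD of 1, the endpoint part alone is about -0.50 at 45% vs 35%, with a range from about -1.0 to +0.26. These figures only illustrate that the artefact can be large and can go either way; they do not estimate what the cohorts will show.

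**What to change.** 1. **Outcome section.** Correct the sentence so that NEWS2+ is named as predicting ICU admission or death within 14 days of admission. Bring the wording in Selection of COVID-19 prognostic models, which says the candidate models predict mortality, into line.
2. **NEWS2+ where possible.** In hospital cohorts that record ICU admission and its date, use the 14-day composite for calibration, intercept updating and decision curves.
3. **NEWS2+ elsewhere.** Label the in-hospital mortality analysis as a change of outcome and report discrimination. State that its calibration-in-the-large, and any intercept update, will not be read as an effect of older age.
4. **Decision curve analysis.** Make it agree with Outcome, Assessment of predictive performance and Updating, so that each model's calibration and net benefit use the same stated endpoint. This also needs a stated choice for the other models whose Table 1 outcome is not in-hospital mortality, such as CURB-65 (30 days) and SOFA (ICU mortality), and for GAL-COVID-19, which has no reported horizon to return to.

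**Cost.** Wording changes and one derived outcome variable. The documents do not say which cohorts hold ICU admission dates, so this has to be checked first. Where the dates are missing, calibration of NEWS2+ on its own endpoint will not be available.

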### Participants

The study participants consist of older individuals (≥ 70 years of age) presenting with highly suspected or reverse transcription polymerase chain reaction (RT-PCR) confirmed COVID-19 from March 2020 to December 2020 in hospital, primary care, and nursing home settings.

Before the widespread use of the RT-PCR test for COVID-19 diagnosis, participants were included using proxy criteria. In the hospital cohorts (CliniCo, COVID-OLD, COVID-PREDICT), the reported respiratory diseases that had COVID-like symptomology are used as an inclusion criterion until 31 March 2020. From April 2020 onwards, a confirmed RT-PCR test for COVID-19 is used as an inclusion criterion. In the primary care cohorts (PHARMO and JHN/ANH/AHA), the participants are included based on free text information and reports of respiratory infections. From June 2020 onwards, ICPC R83.03 for COVID-19 infection is used as an inclusion criterion. The nursing home cohort (Ysis) used RT-PCR as an inclusion criterion. Only participant data on the first presentation or admission of COVID-19 will be included. In the three hospital cohorts, admissions with a duration fewer than 7 days between discharge and readmission will be considered a single hospital admission.

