#### Sensitivity analysis

Two sensitivity analyses will be performed to assess the variation in the predictive performance of the eight COVID-19 prognostic models when implemented in different time periods: January 2021 to December 2021 and March 2020 to December 2021. Additionally, predictive performance in estimating the 90-day mortality risk will be evaluated in cohorts that have data available on this outcome (CliniCo, COVID-PREDICT, PHARMO, JHN/ANH/AHA, Ysis).

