## Discussion

This external validation study will assess the predictive performance of pre-existing clinical and COVID-19-specific prognostic models in the older population. Our study will reveal the validity of these COVID-19 prognostic models in one of the most vulnerable populations, the older population, as well as give insight into the requirements for tailored prediction models for the older population in future COVID-19 waves or pandemics.

While previous studies have largely focused on external validation of COVID-19 prediction models in the general adult population [14, 40, 41], this external validation study will focus on evaluating the performance of existing COVID-19 prognostic models specifically in the older population which represents the highest proportion of hospitalized COVID-19 patients and the highest mortality [3].

External validation in multiple cohorts across different healthcare settings allows for the assessment of between-setting heterogeneity in predictive performance and applicability at different points of care in older COVID-19 patients. This is one of the first studies to evaluate prognostic models for COVID-19 disease in individuals living in nursing homes.

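### The main cross-setting evaluation of the GAL model counts in-hospital deaths in hospitals and 28-day deaths elsewhere, so hospital versus non-hospital differences in calibration mix setting with outcome definition

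*Protocol article*

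**What the plan says.** The Outcome section of the protocol article sets two definitions. For hospitals: "In all three hospital cohorts, the outcome is defined as in-hospital mortality". For the rest: "In the primary care and nursing home cohorts, the outcome is defined as 28-day mortality".

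GAL is the one model applied everywhere. The Statistical analysis section states: "The performance of the GAL-COVID-19 model is assessed across the three healthcare settings". The end of the Background gives assessment across settings as the reason for evaluating one model in all of them. The Discussion says that validation in several cohorts across settings "allows for the assessment of between-setting heterogeneity in predictive performance".

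Table 1 gives GAL's predicted outcome as "Mortality (no prediction horizon reported", with derivation in primary care.

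Calibration-in-the-large and calibration slope are planned for GAL in each cohort (Assessment of predictive performance). Models that show miscalibration receive an intercept update (Updating). The Sensitivity analysis section adds 90-day mortality in "cohorts that have data available on this outcome (CliniCo, COVID-PREDICT, PHARMO, JHN/ANH/AHA, Ysis". Challenges and limitations mentions differing inclusion and predictor definitions, but not differing outcomes.

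**The concern.** In the main analysis the outcome definition changes exactly where the setting changes from hospital to non-hospital. A patient discharged alive who dies at home on day 12 is a non-event in a hospital cohort, but an event in primary care or a nursing home. A patient who dies in hospital on day 40 is an event in a hospital cohort, and the same time of death is a non-event under the 28-day definition.

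Calibration-in-the-large depends directly on how deaths are counted. If GAL appears to overpredict in hospitals relative to nursing homes, the reader cannot tell from the main analysis how much is poor transport to the hospital setting and how much is the counting rule. An intercept update would absorb both, and the updated versions of GAL would then predict different quantities in different cohorts. The c-statistic, calibration slope and net benefit are also exposed, though less directly.

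**Working it through.** The plan states no figure for this point, so there is nothing to reproduce. The check sets the definitions side by side and then gauges a plausible size.

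**Definitions by cohort** (Table 2, Outcome, Sensitivity analysis)

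| Cohort | Setting | Main outcome | Listed for 90-day analysis |
|---|---|---|---|
| CliniCo | Hospital | In-hospital death | Yes |
| COVID-PREDICT | Hospital | In-hospital death | Yes |
| COVID-OLD | Hospital | In-hospital death | No |
| PHARMO | Primary care | 28-day death | Yes |
| JHN/ANH/AHA | Primary care | 28-day death | Yes |
| Ysis | Nursing home | 28-day death | Yes |

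Two things follow. In the main analysis no hospital cohort shares an outcome with any non-hospital cohort, while primary care and nursing home share theirs. The 90-day outcome is common to five of six cohorts and to all three settings.

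The Participants section merges admissions fewer than 7 days apart. That brings in a death after early readmission, but not a death outside hospital after discharge.

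**Illustrative size** (inputs assumed, none from the documents)

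Let m be 28-day mortality in hospital patients and f the share of those deaths that occur after discharge. Suppose GAL were perfectly calibrated for 28-day death. Counting only in-hospital deaths by day 28 gives an observed risk of m(1 - f). The approximate shift in calibration-in-the-large, ignoring the spread of the linear predictor, is

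logit(m(1 - f)) - logit(m).

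| m | f = 0.10 | f = 0.20 | f = 0.30 |
|---|---|---|---|
| 0.20 | -0.130 | -0.272 | -0.429 |
| 0.30 | -0.147 | -0.305 | -0.478 |
| 0.40 | -0.170 | -0.348 | -0.539 |

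For example, with m = 0.20 and f = 0.10 the observed risk is 0.18, and ln(0.18/0.82) - ln(0.20/0.80) = -1.516 + 1.386 = -0.130.

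**Offset.** In-hospital deaths after day 28 count as events in hospitals. If they equal a fraction g of the 28-day deaths, the observed risk becomes m(1 - f + g). The shift disappears when g = f and turns positive when g > f. The documents give neither f nor g, so the net direction is open.

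**Against sampling error.** In a hospital cohort of exactly the stated 754, the standard error of calibration-in-the-large is roughly 1/sqrt(754 × m(1 - m)). This is 1/sqrt(754 × 0.16) = 0.091 at m = 0.20 and 1/sqrt(754 × 0.24) = 0.074 at m = 0.40. It also ignores the spread of the linear predictor, which would raise it somewhat. Before the offset, the shifts run from about 1.4 standard errors (0.130/0.091) to about 7.3 (0.539/0.074). A shift in the upper part of this range would be read as miscalibration.

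**The case against.** The strongest reply is that the protocol already holds the remedy. A reader might infer from the Outcome section that setting and outcome definition cannot be separated at all. The documents do not support that: the planned 90-day analysis applies one fixed horizon in every setting, and primary care and nursing homes share the 28-day outcome. What remains is that the 90-day analysis is labelled a sensitivity analysis, omits COVID-OLD, and is nowhere named as the basis for the cross-setting reading of GAL.

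The choice of in-hospital mortality also has a visible rationale. Table 1 gives it as the predicted outcome of the 4C, Xie and Wang models, and it is the one outcome stated for all three hospital cohorts. This justifies keeping it for the hospital models. It does not tie GAL to it, since GAL has no reported horizon. For the same reason, 28 days cannot be called GAL's correct horizon either.

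Performance is evaluated in each cohort separately, with no formal between-setting test and no setting-level update described. That is correct, but the Discussion's claim about between-setting heterogeneity can only rest on comparing those cohort results.

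A reader might also want to add case definitions to the criticism. Early primary care inclusion is indeed loose: "the participants are included based on free text information and reports of respiratory infections". For hospitals, however, "From April 2020 onwards, a confirmed RT-PCR test for COVID-19 is used as an inclusion criterion", and the nursing home cohort also uses RT-PCR, so these two largely agree. Challenges and limitations openly acknowledges the inclusion differences and argues that they resemble practice. That part is disclosed and is not pressed here. A rerun in confirmed cases only would not settle it: the settings would cover different calendar windows, and the protocol does not say that the primary care code used from June 2020 requires laboratory confirmation.

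**Conclusion.** The point holds for the hospital versus non-hospital comparison of GAL in the main analysis. Differences in calibration there, and any intercept update, combine setting with outcome definition, and the protocol does not list this among its limitations. The primary care versus nursing home contrast has no such problem, and the results for each cohort remain valid for the outcome used there.

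The range of -0.13 to -0.54 on the logit scale rests wholly on assumed inputs (10-30% of 28-day deaths after discharge, 28-day mortality of 20-40%) and stands before the offset from late in-hospital deaths. It shows that the effect could matter. It is not an estimate, and its net sign is unknown. The change is worth making because it is cheap and the common-horizon data are already planned for.

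**What to change.** For GAL only, state that between-setting conclusions rest on one fixed horizon applied identically in every cohort compared. The documented option is the planned 90-day mortality in CliniCo, COVID-PREDICT, PHARMO, JHN/ANH/AHA and Ysis. Use 28-day mortality instead only if it can be derived in all five; the protocol does not say that 28-day status is held in the two hospital cohorts. Do not mix 28-day and 90-day outcomes within one comparison, since that would recreate the mismatch.

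Keep in-hospital mortality for the hospital models and for COVID-OLD. Add the outcome difference to Challenges and limitations, and say there that main-analysis differences in GAL calibration between hospital and other cohorts are not to be read as setting effects alone.

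The 90-day option needs no new data, only a change in the role of a planned analysis and a few sentences. The price is that COVID-OLD drops out of the cross-setting comparison, leaving two hospital cohorts. Because GAL has no reported horizon, the 90-day results should be read for the contrast between settings rather than for the absolute level of calibration.
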